## Abstract

**Background:**

Prevalence of musculoskeletal pain is high among eldercare workers, and therapeutic exercise has shown to be effective for its management. Although telerehabilitation is an increasingly used alternative for delivering therapeutic exercise, no studies have assessed synchronous group telerehabilitation interventions for the management of musculoskeletal disorders. Thus, the aim of this article is to describe the protocol of a randomized controlled trial that will assess the effects of a videoconference-based group therapeutic exercise intervention on the musculoskeletal pain of eldercare workers.

**Methods:**

This multicenter trial will randomly assign 130 eldercare workers to either a control or experimental group. Participants in the control group will not receive any intervention, and participants in the experimental group will take part in a 12-week remote supervised videoconference-based intervention, consisting of 2 weekly 45-min group sessions. Each session will include 4 sets of 6 progressive resistance exercises for the lower limbs, upper limbs and trunk, performed with bodyweight and elastic bands at moderate-high intensity. Following the 12 weeks, participants in the experimental group will be provided with material for autonomously carry on the therapeutic exercises and advised to continue performing 2 weekly sessions on their own until a 48-week follow-up. Assessments will be performed at baseline, 12 and 48 weeks. Primary outcome will be average pain intensity in the low back during the last 7 days, measured by the 0–10 Numerical Rating Scale. Secondary outcomes will include additional measures of musculoskeletal pain, psycho-affective state, work-related variables, and physical fitness.

**Discussion:**

This will be the first trial, to our knowledge, assessing whether a remote delivery of a group therapeutic exercise intervention via videoconference is effective for reducing the musculoskeletal pain, improving the psycho-affective state and physical fitness, and enhancing the work-related parameters in eldercare workers. If successful, this study will provide innovative tools for implementing effective, scalable and affordable interventions to tackle musculoskeletal disorders in the workplace. It will also highlight the utility of telehealth, and address the importance of therapeutic exercise to manage musculoskeletal pain in a critical population for the future of the aging societies as it is the eldercare workers.

**Trial registration:**

The study protocol was prospectively registered at ClinicalTrials.gov (registration number: NCT05050526) on September 20, 2021.

## Introduction

Eldercare workers are qualified professionals who provide assistance to dependent elderly people at either home or long-term facilities [1]. Demographic projections for the coming decades suggest that the demand for eldercare will at least double by 2050 [2], which makes these professionals a cornerstone for facing the challenge of aging. Taking care of people with moderate or severe disability is a physically demanding task, involving lifting, transferring and other care activities that might lead to an overload of musculoskeletal tissues [3]. Several studies have shown that prevalence of pain is high among eldercare workers [4, 5], with 88% of these professionals reporting at least one body part with work-related musculoskeletal symptoms [6]. Besides, prospective studies with large samples have found that a higher intensity [7] and frequency [8] of pain, as well as a higher number of pain locations [9], are significant risk factors for long-term sickness absence in eldercare workers. Moreover, the presence of pain-related disability and a longer pain duration predict the risk of dropout or job turnover from the eldercare sector [10]. In eldercare workers, musculoskeletal pain is often accompanied by mental health disorders [11–13], which can be exacerbated by the high psychological demands of the profession [14–16].

Physical activity and therapeutic exercise interventions have been shown to be effective in reducing musculoskeletal pain in the general adult population [17], and are included as a first-line treatment in all high-quality clinical practice guidelines with the most up-to-date evidence [18]. Although the biological mechanisms leading to exercise-induced hypoalgesia are not yet fully understood, it seems that the activation of the endogenous opioid system during exercise plays a key role [19]. However, it has been suggested that the endocannabinoid, serotonergic, immune and autonomic nervous systems may also be involved, and there are several psychosocial factors that could influence the exercise modulation of pain [19]. From a biomechanical point of view, improvements in the structure and function of the musculoskeletal system, especially muscle strength, could explain the pain reduction induced by exercise [20].

Telerehabilitation is an increasingly used alternative for remotely delivering health services using telecommunications technologies [21, 22]. Although previous studies reported some positive effects on pain and other health-related outcomes, a recent review stated that it is imperative to conduct high quality clinical trials in order to identify effective telerehabilitation interventions [21]. To the knowledge of the authors, the great majority of internet-based interventions have consisted of websites with content for autonomous consultation, or individual home-videoconference sessions [21–25]. There are two positive experiences showing that synchronous supervised sessions are a feasible way to present group therapeutic exercise interventions in people with chronic obstructive pulmonary disease [26] and older adults [27], but no study has been addressed to assess their effectiveness on musculoskeletal disorders yet. Synchronous supervision and group dynamic could be important for designing exercise programs, as both features are related to higher participant adherence, what may therefore lead to a higher effectiveness [28, 29]. In addition, it could also allow for greater intervention safety, since participants can be continuously monitored for correct execution during exercising.

Thus, a study protocol for a randomized controlled trial was designed with the aim of assessing the effects of a videoconference-based group therapeutic exercise intervention in the medium and long term on the musculoskeletal pain of eldercare workers. Secondary outcomes will include measures related to the psycho-affective state, work-related variables and physical fitness.

## Methods

### Study design

A parallel-assignment, multicenter randomized controlled trial will be carried out. Participants will be recruited from institutions providing eldercare services at home or in long-term facilities. In each of the institutions, and following baseline measurements, participants will be randomly assigned (1:1 ratio) through sealed opaque envelopes to either a control or experimental group by a coin-tossing sequence generation. Assessments of primary and secondary outcomes will be conducted at baseline and at 12 weeks (post-supervised phase) and 48 weeks (post-unsupervised phase) from the beginning of the intervention (Fig. 1). Outcome assessors and data analysts will be blinded to group allocation. Because of the nature of the study, blinding of the participants and the professional supervising the sessions is not possible. The study was designed, and the results will be reported according to the SPIRIT statement [30] and CONSORT guidelines for trials of nonpharmacologic treatment interventions [31].

**Fig. 1 Fig1:**
[figure not shown]
SPIRIT flow diagram for the schedule of enrollment, interventions, and assessments. *Legend*: Con: control group; Exp: experimental group; wk: week

### Inclusion and exclusion criteria

Subjects will be considered eligible for the study if they meet all the following criteria: (a) are formal eldercare workers from eldercare institutions, (b) are ≥ 18 years of age, (c) have ≥ 3 months of experience in the profession, and (d) have an employment contract until at least the date of study completion. Participants will be excluded if (a) they are pregnant or (b) their participation is considered contraindicated according to the American College of Sports Medicine’s exercise preparticipation health screening guidelines [32].

### Control group

Participants in the control group will not receive any intervention and will be instructed to continue with their usual lifestyle.

### Experimental group

#### Supervised phase

Participants in the experimental group will take part in a 12-week exercise intervention, consisting of two videoconference-supervised sessions per week of 45 min each. A minimum interval of 48 h will be ensured between sessions. The sessions will be carried out in groups of a maximum of 10 participants, implemented in the workplace but outside of working hours, and remotely supervised in real-time by a professional with previous experience in delivering group exercise sessions. Real-time videoconference platforms such as Webex (Cisco Systems, Milpitas, USA) will be used, and audio and video will be continuously shared between participants and trainer to allow complete bidirectional feedback (Fig. 2).

**Fig. 2 Fig2:**
[figure not shown]
Setting up of the videoconference-supervised exercise sessions. *Legend*: **A** workplace setting in a participating nursing home; **B** setting of the professional supervising the session; **C** screenshot of a videoconference session

The technical content of the program is based on a literature review, authors’ expertise and field experience, as well as on the results of a previous pilot trial that we carried out between January and March 2020 with 20 eldercare workers [33], that allowed us to define the exercises, intensities, and feasibility of a program addressed for reducing the musculoskeletal pain in this population. Intervention details are reported based on the Template for Intervention Description and Replication (TIDieR) Checklist [34]. Sessions will start with a warm-up (5–10 min), including joint mobility and aerobic activation exercises focused on increasing heart rate. The main part of the session will consist of resistance exercises (30 min) performed at moderate-high intensity. In total, 9 exercises will be performed throughout the program (Fig. 3). In each session, 4 sets of 6 resistance exercises will be performed, with a 2-min active rest (dynamic stretching and breathing exercises) between sets. Exercises will be systematically varied between sessions so that each of them is evenly performed during the program. In each set, exercises for the different major muscle groups will be alternated in a circuit manner (e.g., lower limb, upper limb, trunk, lower limb, upper limb, trunk) (Table 1). Unilateral exercises will be alternated between sets so that both sides of the body are evenly worked in each session. Exercises will be performed with minimal equipment, combining body-weight and 2-m-long elastic band exercises. Three progression levels will be set for each of the exercises: progression 1 (weeks 1–4), progression 2 (weeks 5–8) and progression 3 (weeks 9–12) (Fig. 3). All participants will start in progression 1, and transition to a subsequent progression will only be allowed if the participant completes ≥ 4 sessions in the previous progression level. Progression levels are achieved by modifying the exercise technique (e.g., increasing the force lever) or utilizing elastic bands of different resistances (1.7, 2.1 and 2.6 kg at 100% elongation for progressions 1, 2 and 3, respectively) (Fig. 3). One minute will be dedicated to the completion of each exercise (including work and rest times), and within each progression level, the work:rest ratio will augment from 30:30 to 45:15 s, thus adding 5 s of work and reducing 5 s of rest each week (Fig. 4). Participants will be asked and monitored to work at a rate of perceived exertion between 3 (moderate) and 5 (strong) on the Borg's CR-10 scale [35] and not to reach failure in any of the exercises. If any of the exercises cause intolerable pain, the 4-stage exercise adjustment model proposed by Jakobsen et al. [36] will be used: (1) reduce loading intensity (e.g., returning to a previous progression level or even performing the exercise without external resistance), (2) reduce movement velocity, (3) reduce range of motion, and (4) interrupt exercise. If an exercise needs to be interrupted, it will be replaced by a pain-free exercise focused on the same muscle group. Sessions will finish with a cool-down (5–10 min), including static stretching and breathing/relaxing exercises. Daily attendance will be recorded by the professional who supervises the sessions. This professional will also collect information on the completion and intensity of each participant's training in each session. Adherence will be reported as the percentage of sessions in which participants performed the planned training regarding completion and intensity (i.e., 24 sessions = 100% of adherence) [37].

**Fig. 3 Fig3:**
[figure not shown]
Resistance exercises performed in the program

**Table 1 Tab1:** Example of the scheduling of the intervention for the 7^th^ week

Objective	Session 1	Session 2
**Warm-up** (5–10 min)	Joint mobility	Joint mobility
	Aerobic activation	Aerobic activation
**Resistance training** (30 min) 4 sets with 2-min active rest between sets	1. Squat (+ 3 s isometric pause) 40’’	1. Pull-apart (2.1 kg elastic band) 40’’
	*Rest 20’’*	*Rest 20’’*
	2. Arm raise (2.1 kg elastic band) 40’’	2. Bird dog (arms and legs: regular) 40’’
	*Rest 20’’*	*Rest 20’’*
	3. Dead bug (legs only) 40’’	3. Glute bridge (unilateral: short lever) 40’’
	*Rest 20’’*	*Rest 20’’*
	4. Glute bridge (unilateral: short lever) 40’’	4. Biceps curl (2.1 kg elastic band) 40’’
	*Rest 20’’*	*Rest 20’’*
	5. Pull-apart (2.1 kg elastic band) 40’’	5. Lateral plank (medium lever) 40’’
	*Rest 20’’*	*Rest 20’’*
	6. Bird dog (arms and legs: regular) 40’’	6. Reverse lunge (dynamic) 40’’
**Cool-down** (5–10 min)	Static stretching	Static stretching
	Breathing/relaxing exercises	Breathing/relaxing exercises

**Fig. 4 Fig4:**
[figure not shown]
Progression of the exercises during the 12 weeks of intervention

#### Unsupervised phase

When the 12-week supervised sessions are finished, participants in the experimental group will be encouraged to continue performing 2 weekly sessions on their own until the 48-week follow-up. To facilitate this autonomous training, we will create supportive material for the sessions that will include two 45-min recordings with the equivalent content to a session planned for the 12^th^ week, explanatory videos of the 9 exercises performed in the supervised program and their corresponding progressions, as well as written instructions about how to perform the exercises. To record completion in this unsupervised phase, participants will be asked, every 12 weeks and until the 48-week assessments (Fig. 1), the following questions: (a) in the last 12 weeks, in how many weeks did you perform the exercises? (0–12) and (b) on average, in each of those weeks in which you performed the exercises, on how many days did you perform them? (0–7). The result of the multiplication of both answers will be considered the number of performed unsupervised sessions. In this case, self-reported completion will be calculated as a percentage of performed sessions (i.e., 72 sessions = 100% completion in the unsupervised phase).

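### The unsupervised completion percentage has no cap: it can reach 350%, and a participant who stopped for two thirds of the phase can still score 100%

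*Protocol article*

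**What the plan says.** The relevant rules are in the protocol article, Methods, Experimental group.

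- **Advice (Unsupervised phase).** Participants are "encouraged to continue performing 2 weekly sessions on their own until the 48-week follow-up".
- **Data collected (Unsupervised phase).** "participants will be asked, every 12 weeks and until the 48-week assessments", two questions are put: the number of weeks with exercise in the preceding 12 (range 0–12), and the average number of days with exercise in those active weeks (range 0–7).
- **Numerator (Unsupervised phase).** "The result of the multiplication of both answers will be considered the number of performed unsupervised sessions".
- **Denominator (Unsupervised phase).** "72 sessions = 100% completion in the unsupervised phase".
- **Supervised phase, for contrast.** Adherence is the share of sessions performed as planned in completion and intensity, with "24 sessions = 100% of adherence".
- **Reporting (Statistical analysis plan section).** Continuous data are summarised as mean (standard deviation).

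No limit on the unsupervised count is stated per week, per 12-week window or overall.

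**The concern.** The denominator is the advised programme. The numerator is all self-reported exercise days, including those beyond the advice. A ratio of the two measures exercise volume relative to the advice, but the article calls it completion and fixes a 100% point. A reader will take 100% to mean that the advised programme was followed to the end, and the formula does not guarantee that for a person or for the arm.

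The unsupervised phase covers 36 of the 48 weeks and 72 of the 96 advised sessions (24 + 72). This percentage is the only exposure measure the article describes for it. Week 48 is one of the two periods analysed. If the week-48 effect is weak, readers will look at completion to judge whether the programme failed or was not used. A figure raised by extra sessions could point them to the wrong explanation.

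**Working it through.** **Inputs.** Advised frequency: 2 sessions a week (Unsupervised phase). Assessments are at "12 weeks (post-supervised phase) and 48 weeks (post-unsupervised phase) from the beginning of the intervention" (Study design). Recall window: 12 weeks. Ranges: weeks 0–12, days 0–7.

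**Step 1. Reproduce the article's figure.** Phase length = 48 − 12 = 36 weeks. Advised sessions = 2 x 36 = 72. This matches the stated denominator.

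**Step 2. Ceiling.** Number of windows = 36/12 = 3. Maximum per window = 12 x 7 = 84. Maximum total = 3 x 84 = 252. Maximum completion = 252/72 = 350%. The article does not say in words that the three products are added, but a denominator of 72 requires it.

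**Step 3. One participant.** Weeks 12 to 24 at 6 days a week: 12 x 6 = 72. Weeks 24 to 48: 0. Completion = 72/72 = 100%, with no exercise in 24 of 36 weeks. Counting at most 2 sessions per active week gives 12 x 2 = 24, and 24/72 = 33%.

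**Step 4. The arm mean.** Assume a share *s* of the arm exercises *d* days a week for all 36 weeks and everyone else does nothing. Each active participant scores 36*d*/72 = *d*/2, so the mean is *s* x *d*/2. It equals 100% when *s* = 2/*d*. With a cap at 2 a week, the mean is simply *s*.

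| Days a week (*d*) | Score of an active participant | Share giving an uncapped mean of 100% | Capped mean at that share |
|---|---|---|---|
| 2 | 100% | 100% | 100% |
| 3 | 150% | 67% | 67% |
| 4 | 200% | 50% | 50% |
| 5 | 250% | 40% | 40% |
| 7 | 350% | 29% | 29% |

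The first row is the no-inflation case: if nobody exceeds 2 days a week, the capped and uncapped figures agree.

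**Step 5. Would the SD show it?** For the planned 65 participants in the experimental arm:

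- 33 at 4 days a week and 32 at zero: mean 102%, SD 101, capped mean 51%.
- 19 at 7 days a week and 46 at zero: mean 102%, SD 160, capped mean 29%.

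The large SD signals wide spread. It does not tell the reader what proportion stopped.

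**The case against.** The strongest reply is that nothing is miscalculated. The 72 is right, the formula gives a count of sessions performed, and a value above 100% simply means more sessions than advised. That stands as far as the arithmetic goes; the objection here is to using that ratio as a measure of completion.

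Second, the figure enters no stated inference. A reader might infer that it distorts the main result or decides who is in the per-protocol set. The documents do not support either. The primary analysis is intention-to-treat regardless of adherence. The per-protocol threshold of 50% is set on adherence, a term the article defines on the 24 supervised sessions, whereas the unsupervised phase uses completion. This point stands and limits the importance of the issue.

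Third, a reader might conclude that people who exercise a great deal will hide those who stopped. That is only possible, not established: it depends on how participants answer, and the documents give no distribution of answers. The answers are also collected separately in each window, so stopping would appear as zeros in later windows if those were reported. This also stands.

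Fourth, the supervised measure cannot exceed 100% while this one can. A reader might infer that the plan compares them wrongly, but the article makes no such comparison and labels the unsupervised figure as self-reported.

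Finally, a truncation rule could sit in a fuller analysis plan, and the Discussion already lists self-reported compliance as a limitation. This does not remove the point. The article itself fixes the numerator, the denominator and the 100% mark, so the rule can be judged as written. The stated limitation concerns self-report, not values above 100% or one person's excess offsetting another's absence.

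**Conclusion.** The point holds as a defect in a stated derivation. As written, unsupervised completion can reach 350%, and a participant can score 100% after stopping for 24 of the 36 weeks. At arm level the possible inflation runs from none (nobody above 2 days a week) to a mean of 100% with as few as 29% of participants active (all at 7 days, the rest at zero). These arm-level figures rest on assumed answer patterns and show a range, not a forecast.

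The consequence is confined to one descriptive figure in the experimental arm, which matters because it is needed to interpret the 48-week result. The sample size, the intention-to-treat analysis and, on the article's wording, the per-protocol set are unaffected.

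**What to change.** Keep both questions and change the derivation before analysis:

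1. In each 12-week window, compute sessions counting towards completion as weeks x min(average days, 2), at most 24. Sum the three windows, at most 72, and divide by 72.
2. State that this is an upper bound. The days answer is an average over active weeks, so a week above 2 days can still offset a week below 2 within the same window.
3. Report the uncapped product separately, named as exercise volume.
4. For each window, give the proportion of participants at zero and the proportion at 50% or more, alongside the mean.

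The limit should apply per week and not only per window. Six weeks at 4 days would score 24/24 under a window cap alone, against 6 x 2 = 12 of 24 under the rule above.

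The cost is a few lines of wording and a completion figure that can only be the same or less favourable. The questions, the assessment schedule and the exercise advice do not change, and the answers needed are already planned for collection.

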### Outcomes

#### Baseline descriptive data

Participants will report by a self-administered written questionnaire the following descriptive data at baseline: date of birth, sex (male/female), height (cm), mass (kg), marital status (single/married/divorced/widower), educational level (primary/secondary/tertiary education), number of children (n), children cohabiting at home (no/yes), care for dependent people outside the work environment (no/yes), working hours (hours/week), experience in the profession (years), type of work shift (rotative/fixed), night shift (no/yes), alcohol consumption (never/monthly or less/2–4 times a month/2–3 times a week/ ≥ 4 times a week) [38], tobacco consumption (daily/less than daily/not at all) [39], recreational physical activity (1–8) [40], and regular resistance-exercise training (no/yes).

